[figure not shown]

**Investigational drug:**

HQP1351, olverembatinib

**Chemical name of investigational drug:**

3-[(1H-pyrazolo[3,4-b]pyridin-5-yl)ethynyl]-4-methyl-N-{4-[(4-methylpiperazin-1-yl)methyl]-3-(trifluoromethyl)phenyl}benzamide

**Study Title:**

A Phase I Clinical Study of the Safety, Pharmacokinetics and Pharmacodynamics of HQP1351 in Patients with Advanced Gastrointestinal Stromal Tumors and Other Solid Tumors

**Study site: Multicentre****Estimated recruitment duration (year):**

4 to 5 years

**Phase:**

Phase I

**Objectives:****Primary objective:**

- To assess the safety and tolerability of HQP1351 in different dose groups in the treatment of patients with advanced gastrointestinal stromal tumors (GIST) or other solid tumors, and determine the recommended Phase II dose (RP2D).

**Secondary objectives:**

- To preliminarily assess the efficacy of HQP1351 in patients with advanced GIST or other solid tumors.
- To assess the pharmacokinetics (PK) of HQP1351.

**Exploratory objective:**

- To explore biomarkers related to the efficacy of HQP1351 monotherapy.

**Study design:**

This is an open-label, multicenter, Phase I clinical trial which is designed to determine the safety and tolerability of HQP1351 in patients with advanced GIST and other solid tumors,

[figure not shown]

to determine the RP2D, and to assess the preliminary efficacy of HQP1351 in patients with GIST and other solid tumors.

As of February 2021, HQP1351 has undergone a total of 9 clinical studies, and preliminary results from the Phase I and Phase II clinical trials that have been conducted show a favorable safety profile up to dose of 50 mg QOD. HQP1351 (olverembatinib tablets) has been granted conditional marketing authorization from the National Medical Products Administration on November 24, 2021 (approval number: NMPA H20210048). It is indicated for the treatment of "adult patients with tyrosine kinase inhibitor (TKI)-resistant chronic phase chronic myeloid leukemia (CML-CP) or accelerated-phase CML (CML-AP) harboring the T315I mutation as confirmed by a validated diagnostic test", and the recommended dose is 40 mg QOD.

This study is initially designed as a Phase I study with standard 3+3 dose escalation. Based on the study results of HQP1351 SJ-0002 in CML patients and the consensus reached at the SJ-0003 kick-off meeting with the investigator, this study will explore the safety in the 30 mg, 40 mg, and 50 mg dose groups in parallel, and 10 subjects will be enrolled by means of randomization at each dose level using the IWRS. After preliminary adult data are available, adolescent subjects with advanced and/or metastatic wild-type GIST will be included. The dosage for adolescents is based on the adult dose and the selected dose will be adjusted according to their body weight. If the subject's body weight is  $\geq 40$  kg, the dose of 40 mg QOD will be given based on the adult dose. If the subject's body weight is  $\geq 30$  kg and  $< 40$  kg, the dose of 30 mg QOD will be given. If the subject's body weight is  $\geq 20$  kg and  $< 30$  kg, 20 mg QOD will be given. Based on the safety data from 9 clinical studies that have been conducted with HQP1351 and the safety and efficacy data of 36 patients already enrolled in this study, 40 mg QOD is selected as the dosage for non-randomized adult subjects after discussion between the investigator and the sponsor.

Subjects enrolled in the Phase I study with standard 3+3 dose escalation who have received at least one cycle of HQP1351 after this protocol amendment takes effect, and have not experienced related or possibly related Grade  $\geq 2$  toxicity nor have tumor progression, may receive a higher dose of HQP1351 upon their own informed consent after discussion between the investigator and the sponsor. The subject will continue to be followed up according to the revised protocol, but will not be included in the number of randomized subjects.

Eligible subjects after screening will orally receive HQP1351 tablets every 2 days continuously in 28-day cycles until PD, intolerable toxicity, death, or termination of treatment for any other reason. If a subject is assessed to have PD according to the RECIST v1.1 criteria, but the investigator determines that the subject will benefit from continuing the study, then the subject may continue to take HQP1351 and undergo safety follow-up yet no more efficacy follow-up after PD is documented. During medication, subjects will not

[figure not shown]

receive other antitumor study drugs, marketed drugs, or treatment methods other than HQP1351. Symptomatic (including those directed at controlling symptoms resulting from the patient's malignancy) and supportive treatments are allowed.

In the standard 3+3 dose escalation part of this study, blood samples from subjects in Cycle 1 will be collected for the PK analysis of HQP1351. In the randomized part, 1-3 study sites will be selected to collect the blood samples of the first 3 enrolled subjects in each dose group in Cycle 1 for the PK analysis of HQP1351. If for any reason complete PK samples are not obtained from the first 3 subjects, they will be replaced by subjects subsequently enrolled in the dose group until complete PK samples are obtained from 3 subjects. PK blood samples will be collected from all non-randomized adult subjects receiving a fixed dose of 40 mg QOD for PK analysis. PK blood samples will be collected from all adolescent subjects for PK analysis.

Blood and tumor tissue samples will be collected from all subjects for biomarker assessment.

All subjects will undergo efficacy assessment every 8 weeks during treatment, along with assessment of safety information such as AEs and laboratory tests.

**Number of subjects (planned):**

About 50-60 subjects are expected to be included in this study.

**Inclusion criteria:**

Subjects will be eligible for the study if they meet all of the following criteria:

1. Aged  $\geq 12$  years, male or female.
2. Advanced and/or metastatic GIST or other solid tumors, confirmed by histology and/or cytology. Among them, GIST patients must have primary resistance to imatinib (tumor progression within 6 months after first-line use of imatinib, or immunohistochemical presence of SDHB expression deletion or NF1 mutation) or have failed treatment with imatinib or imatinib plus at least one other TKI (following initial imatinib or other TKI treatment for more than 6 months, the subject has tumor progression again after achieving a response or stable disease).
3. ECOG score  $\leq 2$ .
4. Life expectancy of  $\geq 3$  months.
5. Hematologic function as outlined below:
  - Absolute neutrophil count (ANC)  $\geq 1.5 \times 10^9/L$  (ANC achieved by colony-stimulating factors will not be allowed);
  - Platelet count  $\geq 100 \times 10^9/L$  (baseline platelet count achieved by blood transfusion or thrombopoietic growth factor will not be allowed);

[figure not shown]

- Hemoglobin  $\geq 90$  g/L

Note: If hemoglobin is stable for 14 days after transfusion (reduced by no more than 10 g/L), transfusion is allowed, and the use of erythropoiesis-stimulating agents (ESAs) is allowed;

- Serum albumin  $\geq 30.0$  g/L;
- Serum lipase  $\leq 1.5 \times$  upper limit of normal (ULN);
- Serum amylase  $\leq 1.5 \times$  ULN;

6. Hepatic and renal function:

- Serum creatinine  $\leq 1.5 \times$  ULN; or serum creatinine  $> 1.5 \times$  ULN, and creatinine clearance  $\geq 50$  mL/min;
- Serum total bilirubin  $\leq 1.5 \times$  ULN;
- Aspartate aminotransferase (AST) and alanine aminotransferase (ALT)  $\leq 2.5 \times$  ULN ( $\leq 5 \times$  ULN in the presence of liver metastasis);

7. Cardiac function index:

- Troponin (I or T)  $\leq$  ULN;
- Ejection fraction (EF)  $> 40\%$ ;
- QTc interval on electrocardiogram (corrected by Bazett's formula): male  $\leq 450$  ms and female  $\leq 470$  ms.

8. Women of childbearing potential should have a negative serum pregnancy test within 7 days prior to the first dose of the study drug.

9. Men and women of childbearing potential (postmenopausal women must be amenorrheic for at least 12 months to be considered of non-childbearing potential) and their partners are willing to take protocol-specified effective contraceptive measures from signing the informed consent form to at least 30 days after the last dose of the investigational product.

10. Able to understand and voluntarily sign the written ICF before any study-specific procedures.

11. Subjects must be willing and able to complete study procedures and follow-up examination.

**Exclusion criteria:**

Subjects who meet any of the following criteria are not eligible for this study:

1. Subjects who have received antitumor cytotoxic chemotherapy, biologic drug therapy (such as monoclonal antibodies), immunotherapy (such as interferon), or radiotherapy

[figure not shown]

- within 28 days prior to the first dose or less than 5 times the half-life.
2. Subjects who have received tyrosine kinase inhibitor (TKI) treatment within 14 days prior to the first dose.
  3. Subjects who have received other study drugs within 14 days prior to the first dose.
  4. Subjects who have not recovered from adverse events (except alopecia) (> NCI-CTCAE v4.03 grade 1) due to prior treatment.
  5. Malabsorption syndrome or other diseases affecting oral drug absorption.
  6. Clinically significant, uncontrolled, or active cardiovascular diseases, including but not limited to history of myocardial infarction; history of unstable angina; history of congestive heart failure or left ventricular ejection fraction (LVEF) below the lower limit of normal within 6 months; history of atrial arrhythmia judged by the investigator to be of important clinical significance; history of ventricular arrhythmia, etc.
  7. Hypertension inadequately controlled by antihypertensive drugs (systolic pressure >150 mmHg or diastolic pressure >90 mmHg).
  8. Subjects who need to take drugs that has a known potential to cause ECG QT prolonged.
  9. Pulmonary arterial systolic pressure >35 mmHg as indicated by Echocardiography.
  10. Subjects who have serious cardiovascular diseases during prior TKI use.
  11. Hypertriglyceridemia that is difficult to control.
  12. Major surgery, open biopsy (except intravenous catheter placement or bone marrow biopsy), or major traumatic injury within 14 days prior to the administration of study drug.
  13. Arterial thrombosis or embolic events such as cerebrovascular accidents (including transient ischemic attacks), or pulmonary embolism or venous thrombosis events within 6 months prior to the administration of study drug, such as deep vein thrombosis within 3 months prior to the administration of study drug.
  14. Subjects who require concomitant immunosuppressive therapy, other than corticosteroids prescribed for a short course of therapy.
  15. Subjects with brain metastases.
  16. Patients with other primary malignant neoplasm within recent 3 years (patients who are cured for  $\geq 5$  years, or with completely resected non-melanoma skin cancer, or successfully treated carcinoma in situ, or prostatic carcinoma under control will be included).
  17. Active symptomatic viral infections (including known HIV infections, viral hepatitis (B or C, etc.), syphilis, etc.).

[figure not shown]

18. Subjects who are known to be allergic to any components of the investigational drug or its analogues.
19. Female subjects who are pregnant or breastfeeding, or who expect to become pregnant during the study period.
20. Subjects who have any symptom or disease that, according to the opinions of the investigator or sponsor, would comprise their safety or interfere with the safety assessment of the investigational drug.

**Dosing regimen**

HQP1351 Tablets will be orally administered at a dose of 10 mg/tablet every two days in a 28-day cycle. Randomized subjects will randomly receive 30 mg QOD, 40 mg QOD, and 50 mg QOD dosing regimens. Non-randomized adult subjects will receive a 40 mg QOD dosing regimen. The dosage for adolescents is based on the adult dose and the selected dose will be adjusted according to their body weight. If the subject's body weight is  $\geq 40$  kg, the dose of 40 mg QOD will be given based on the adult dose. If the subject's body weight is  $\geq 30$  kg and  $< 40$  kg, the dose of 30 mg QOD will be given. If the subject's body weight is  $\geq 20$  kg and  $< 30$  kg, 20 mg QOD will be given.

**Duration of treatment:**

Subjects will receive treatment until PD, observation of intolerable toxicity, death, or termination of treatment for any other reason. If a subject is assessed to have PD according to the RECIST v1.1 criteria, but the investigator determines that the subject will benefit from continuing the study, then the subject may continue to take HQP1351 and undergo safety follow-up yet no more efficacy follow-up after PD is documented.

**Study endpoints****Primary endpoints:**

- Safety and tolerability assessment will include AEs, physical examination, vital signs, electrocardiogram (ECG) parameters, ECOG performance status score, clinical laboratory tests, and other data.

**Secondary endpoints:**

- To preliminarily assess the efficacy of HQP1351 in patients with gastrointestinal stromal tumors, including overall response rate (investigator-assessed ORR, as per RECIST 1.1), clinical benefit rate (CBR, defined as CR+PR+SD  $\geq 16$  weeks), duration of response (DOR), progression-free survival (PFS), and overall survival (OS).
- To assess the pharmacokinetics (PK) of HQP1351.

**Exploratory endpoint:**

[figure not shown]

- Mutations of *KIT*, *PDGFRa*, and other tumor-related genes and/or expression profiles associated with the efficacy of HQP1351.

**Statistical Methods:**

The latest version of SAS software will be adopted to summarize and tabulate data. Appropriate descriptive statistics (i.e., mean, standard deviation, median and interquartile range, etc.) will be used based on data distribution. Changes from baseline in safety and tumor efficacy measures at each time point during the treatment period and the follow-up period will be compared and assessed. If applicable, the difference in dose level will be analyzed by parametric or non-parametric significance tests.

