## **1.5 HQP1351 Clinical Overview**

As of February 2021, HQP1351 has undergone a total of 9 clinical studies, including 3 Phase I studies (SJ-0002, SJ-0003 and HQP1351CU101), 3 clinical pharmacology studies [HQP1351LC104, HQP1351XC105 and HQP1351XC106 (in healthy volunteers)] and 3 Phase II pivotal studies (HQP1351CC201, HQP1351CC202 and HQP1351CC203). All studies were conducted in China except for HQP1351CU101 and HQP1351XC106 which were conducted in the United States. The Phase I clinical study of HQP1351 for GIST (SJ-0003) is ongoing in Chinese mainland. A total of 36 GIST subjects were enrolled as of January 31, 2021, and treated with HQP1351 orally QOD in 4 dose groups: 3 in the 20 mg dose group, 11 in the 30 mg dose group, 11 in the 40 mg dose group, and 11 in the 50 mg dose group, in 28-day cycles. All subjects were TKI-resistant GIST subjects who had previously been heavily treated. The Phase I study is currently actively enrolling subjects. Of the 36 GIST subjects, 28 have completed at least one efficacy assessment. The results are as follows: 10 subjects had stable disease (SD) and 18 subjects had progressive disease (PD).

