## 7.3 Cycle 1 Visit

### 7.3.1 C1D1 visit

**The following items must be assessed prior to the first dose of HQP1351 (*If laboratory results are available within 7 days prior to the first dose of HQP1351, it is not required to repeat the test*):**

- Vital signs: blood pressure, pulse, respiratory rate and body temperature.
- Physical examination: Disease-related signs can be directly examined.
- Body weight.
- ECOG performance status (See Appendix 1).
- Complete blood count with differential: hemoglobin, hematocrit, red blood cell count, white blood cell count and differential count, and platelet count. White blood cell differential count include neutrophil, lymphocyte, monocyte, eosinophil, and basophil counts (reported as absolute counts).

[figure not shown]

- Serum chemistry: C-reactive protein (CRP), sodium, potassium, magnesium, calcium, phosphorus, chloride, bicarbonate or carbon dioxide, albumin, urea or blood urea nitrogen, creatinine, uric acid, total bilirubin, AST, ALT, glucose, alkaline phosphatase, and triglycerides.
- Coagulation test: prothrombin time (PT) and activity, partial thromboplastin time (PTT)/activated partial thromboplastin time (APTT), fibrin degradation product, fibrinogen quantification, and D-dimer.
- Lipase and amylase
- Urinalysis: Urine glucose, protein, bilirubin, urobilinogen, specific gravity, occult blood, pH value, ketone bodies, nitrite, white blood cells, turbidity, and color. A microscopic analysis will be performed if there is any abnormality in urinalysis.
- 12-lead ECG
- Serum troponin I or T level.
- Collection of PK blood samples
- AEs
- Concomitant medications (from the first dose to 30 days after the last dose)

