## 10 Statistical Analysis

### 10.1 Sample Size Calculation

In the HQP1351 SJ-0002 CML patient study, the MTD has been determined to be 50 mg. But starting from the 12 mg dose group, the drug has shown its efficacy. The study is being expanded at 30 mg, 40 mg and 50 mg to determine the dose groups with the best efficacy/safety ratio. According to the data of HQP1351 SJ-0002 CML patient study, this study has been modified accordingly to randomize subjects into the 30 mg, 40 mg and 50 mg dose groups at the same time, about 10 subjects each.

As of February 2021, HQP1351 has undergone a total of 9 clinical studies, and preliminary results from the Phase I and Phase II clinical trials that have been conducted show a favorable safety profile in the dose range of 50 mg QOD. HQP1351 (olverembatinib tablets) has been granted conditional marketing authorization from the National Medical Products Administration on November 24, 2021, with a recommended dose of 40 mg QOD. Based on the safety data from 9 clinical studies that are conducted with HQP1351 and the safety and efficacy data of 36 patients already enrolled in this study, 40 mg QOD is selected as the dosage for adult subjects after discussion between the investigator and the sponsor. After the randomization of subjects at 30 mg, 40 mg and 50 mg QOD, with about 10 subjects in each group, it is planned to enroll 10-20 subjects in the non-randomized part to further explore the safety and efficacy of the drug, and the final number of enrolled subjects will be determined after discussion between the investigator and the sponsor according to the situation.

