##### **10.4.3 Safety data**

All AEs will be coded according to Medical Dictionary for Regulatory Activities (MedDRA). The frequency (number and percentage of subjects) of subjects experiencing one or more AEs will be calculated and summarized by System Organ Class (SOC) and Preferred Term (PT). All AEs, drug-related AEs (AEs assessed as related or possibly related), AEs and SAEs graded based on NCI CTCAE, and AEs resulting in study withdrawal will be classified and summarized.

AEs and outliers (patient's physical examination results, vital signs, and laboratory results) determined by the investigator to be clinically significant will be summarized and tabulated by dose group.

Deaths, SAEs, and AEs leading to discontinuation of HQP1351 treatment will be listed in detail.

[figure not shown]

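### Dose comparisons on continuous safety measures are planned as significance tests with change from baseline as the scale; a baseline-adjusted estimate with 95% CI, in randomized subjects only, is more precise and needs no new data.

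*Protocol*

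**What the plan says.** Two adjacent sentences in the Synopsis (Statistical Methods) matter here. The first sets scale and occasion: "Changes from baseline in safety and tumor efficacy measures at each time point during the treatment period and the follow-up period" are to be compared. The second sets the tool for comparing doses: if applicable, "the difference in dose level will be analyzed by parametric or non-parametric significance tests". Neither mentions a covariate, an estimate, an interval or a key time point, and neither says which subjects enter the comparison.

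Section 10.1 describes the randomized part as a change to "randomize subjects into the 30 mg, 40 mg and 50 mg dose groups at the same time, about 10 subjects each". It then says "it is planned to enroll 10-20 subjects in the non-randomized part"; under Section 4.1 the adults among these receive 40 mg and the adolescents a weight-based dose. Section 1.5 reports enrolment by January 2021 as "11 in the 30 mg dose group, 11 in the 40 mg dose group, and 11 in the 50 mg dose group", plus 3 at 20 mg.

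Section 10.4.3 names no test: adverse events and clinically significant outlying values "will be summarized and tabulated by dose group". Section 7.3.1 secures the baseline, with a list opening "The following items must be assessed prior to the first dose of HQP1351" that covers vital signs, blood count, chemistry, coagulation, lipase and amylase, ECG and troponin.

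**The concern.** The primary objective is safety and tolerability by dose group and the choice of a recommended Phase II dose. The randomized 30, 40 and 50 mg groups are the only comparison of doses protected from selection. With about 10 subjects in each, that information should be used well. Three features of the wording waste some of it.

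- **Scale.** A change score carries the noise of both measurements at full weight. A model with baseline as covariate gives the baseline only the weight the data support.
- **Output.** A significance test in groups of 10 gives a p-value. If it is not small, it says almost nothing about whether the doses are similarly tolerated. An estimate with an interval shows what differences remain compatible with the data.
- **Population.** Without a limit to randomized subjects, a comparison could pool non-randomized 40 mg subjects, enrolled later and by a different route, with the randomized 40 mg group. Up to 10 to 20 later subjects would then join about 10 randomized ones.

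**Working it through.** The protocol states no alpha, power, SD or effect size for the dose comparison, so there is no figure to reproduce.

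**Inputs**
- n = 10 per dose at 30, 40 and 50 mg (Section 10.1).
- Correlation ρ between baseline and follow-up: not given; assumed from 0.3 to 0.9.
- Equal SD at both times, set to 1: assumed.

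**Step 1. Variance of the 30-versus-50 mg contrast**
- Change score: 2(1 − ρ) × 2/n.
- Dose group plus baseline covariate: (1 − ρ²) × 2/n × (1 + 1/25). The last factor is the cost of estimating the covariate slope with 30 subjects in 3 groups: 1/(30 − 3 − 2) = 1/25.
- Ratio, adjusted over change score: (1 + ρ)/2 × 1.04.

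**Step 2. Numbers**

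| ρ | SE, change score (SD units) | SE, adjusted | Variance ratio | Variance reduction |
|---|---|---|---|---|
| 0.3 | 0.529 | 0.435 | 0.65 × 1.04 = 0.676 | 32% |
| 0.5 | 0.447 | 0.395 | 0.75 × 1.04 = 0.780 | 22% |
| 0.7 | 0.346 | 0.326 | 0.85 × 1.04 = 0.884 | 12% |
| 0.8 | 0.283 | 0.274 | 0.90 × 1.04 = 0.936 | 6% |
| 0.9 | 0.200 | 0.199 | 0.95 × 1.04 = 0.988 | 1% |

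A simulation of 200,000 trials per row gave reductions of 32.4%, 22.1%, 11.4%, 6.0% and 1.2%.

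**Step 3. What an interval would show.** At ρ = 0.5 the 95% half-width is 2.052 × 0.447 = 0.92 SD for the change score (27 df) and 2.056 × 0.395 = 0.81 SD after adjustment (26 df). Either way, differences of most of an SD in both directions can remain compatible with a null-looking result. That is why an interval says more than a p-value here.

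**Step 4. Dose group or linear dose?** With three equally spaced, equal groups, 20 mg times the slope has the same SE as the 50-minus-30 mg mean difference: 20 × √(1/(10 × 200)) = √(2/10) = 0.447 SD when the outcome SD is 1. A slope therefore adds no precision to this contrast. Its advantage is one degree of freedom instead of two. For a linear effect of 0.8, 1.0 and 1.25 SD between 30 and 50 mg, power is 41%, 58% and 77% for the trend, against 31%, 46% and 65% for the two-df test. If only 40 mg differs, by 1.25 SD, the two-df test has 79% power and the slope only about its 5% alpha. So dose group belongs in the main model, with the trend as a supplement.

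**The case against.** The strongest reply is that the protocol commits to less than it seems to. The dose test is conditional (if applicable), it stands in a separate sentence from the one on time points, and a parametric test could be an analysis of covariance or a trend test. Test, covariates and multiplicity are commonly settled in a statistical analysis plan, which is not at hand. All of this stands, and it limits the point to what the Synopsis does fix: the change-from-baseline scale and significance tests as the tool.

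A reader might infer three stronger claims that the documents do not support.

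- **That doses will be tested at every visit.** Every listed blood count, vital sign, chemistry, coagulation, pancreatic enzyme and troponin measure in Cycles 1 and 2 would give 70 + 35 + 89 + 6 + 6 + 3 = 209 tests, about 10 below 0.05 by chance (209 × 0.05 = 10.5). The wording permits this but does not promise it.
- **That the tests will be unadjusted and ignore dose order.** The text is silent on both.
- **That a p-value will drive the recommended dose.** Sections 4.4 and 10.4 make that an overall judgement on safety, tolerability, PK and efficacy, and nothing treats non-significance as equal tolerability.

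It is also fair to say that the gain nearly vanishes for measures that track closely within a subject, and that adjustment does nothing for adverse event rates, response or survival endpoints.

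**Conclusion.** The point holds in a limited form. For continuous safety measures, the scale and tool named in the Synopsis are a weaker choice than a baseline-adjusted estimate with a confidence interval in randomized subjects. The variance gain on the 30-versus-50 mg contrast is about 32%, 22% and 12% at correlations of 0.3, 0.5 and 0.7, and about 6% or less from 0.8 upward. These figures assume 10 subjects per dose, equal SDs at the two times and a linear relation to baseline; the correlations are assumptions. The limit to randomized subjects and the switch from tests to intervals are worth making whatever the correlation. Section 10.4 carries no dose test forward, so this is an improvement in method and does not invalidate the trial's dose decision.

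**What to change.** Replace the Synopsis sentence on dose differences with:

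> In subjects randomized to 30, 40 or 50 mg, any comparison of doses on a continuous safety measure will be made at C2D1 by a model with dose group and the pre-dose baseline value, log-transformed where skewed, and reported as estimated differences between doses with 95% CIs. A linear dose trend may be shown as a supplement. Results at other visits are descriptive, without p-values.

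Adverse event, serious adverse event and efficacy summaries stay as in Section 10.4. C2D1 suits because vital signs, blood count, chemistry, coagulation, lipase and amylase, ECG and troponin are all scheduled then (Section 7.4.1), and it comes early against a mean treatment time of 2.5 months (Section 1.5.2). Echocardiography is first repeated at Cycle 3 Day 1, so ejection fraction stays descriptive unless that visit is named for it.

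The cost is wording only; the data are already collected. The covariate uses one degree of freedom and brings little where baseline correlation is high. The intervals should be read as estimation: counting 10 blood count, 5 vital sign, 18 chemistry, 6 coagulation, 2 pancreatic enzyme and 1 troponin measures gives 42 at C2D1, so about 2 intervals per dose contrast would exclude zero by chance (42 × 0.05 = 2.1).
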